### Recruitment {15}

People who present to ED following a suicide attempt (i.e. the act to take their life) are placed on a journey board, which is reviewed by the MDT. The RA regularly monitors journey boards and communicates with clinical teams to recruit potential participants. Any person identified as a potential participant is discussed during the MDT for appropriateness of recruitment to the ASSIP-CBT Research clinic. Names are then provided to the RA who makes contact with the person (obtain formal consent and recruit into the study). The RA will make every reasonable attempt to follow-up eligible participants to recruit into the study.

The characteristics of patients who were eligible for the trial (both participants and non-participants) are also recorded (e.g. age, gender, reason for declining if applicable).

### Assignment of interventions: allocation

#### Sequence generation {16a}

Randomisation occurs after recruitment. Participants are randomised to either SPP, SPP + ASSIP, or SPP + CBT using random block randomisation (ralloc, Stata 15) with blocks of size 6–15. An intention-to-treat approach will be used for analysis.

#### Implementation {16c}

The RA is responsible for the recruitment of participants and for the assignment of participants to intervention arms. The RA enables the treatment pathway by booking an appointment for the appropriate intervention and informing the ASSIP-CBT Clinician (adult > 25 or youth clinician 16–25, as applicable). The allocation sequence is generated by a biostatistician who is not involved in the recruitment or assessment of participants. Clinical processes and interventions, consumer assessment/documentation, and treatments as well as follow-up, are not affected by the recruitment to the ASSIP-CBT study and are progressed by treating teams as clinically appropriate, as per usual practices.

### Assignment of interventions: blinding

#### Who will be blinded {17a}

Given the clear differences in the therapy interventions, participants and those administering the interventions are not blinded. However, those assessing the outcomes will be blinded to group assignment.

#### Procedure for unblinding if needed {17b}

Not applicable, as those responsible for the healthcare of the participant are not blinded to the group assignment and can inform the statistician to remove data related to a participant with a particular participant number.

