#### Criteria for discontinuing or modifying allocated interventions {11b}

Consumers are made aware (both verbally and written) that they can withdraw consent to participate in the study at any time without any questions asked, or any impact on their ongoing treatment and care. Participants who withdraw from the study are provided with the option of (a) all their collected data being withdrawn from the study or (b) their collected data being used.

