## Statistical methods

### Statistical methods for primary and secondary outcomes {20a}

To determine the effectiveness of additional CBT + SPP or ASSIP+SPP compared with SPP alone, univariate (log rank test) and multivariate Cox proportional hazard shared frailty regression models and multilevel mixed effects parametric models will be used to analyse time to re-presentation for suicide attempts [35]. Time to suicide attempt is measured by calculating the total number of days from the initial presentation (with days of psychiatric admission for some consumers taken into account), to the re-presenting date for a subsequent suicide attempt and may include multiple representations [35]. For participants without a subsequent suicide attempt, the total number of days from enrolment to the last assessment (24 months) will be calculated. All collected demographic and clinical variables will be considered in the model-building process. Variables with *P* ≤ 0.1 on univariate analysis will be included in all combinations and retained in the model if *P* < 0.05. Plausible interactions of retained variables will be tested. Collinearity of potential model variables will be assessed using the variance inflation factor. Where appropriate, the proportional hazards assumption will be tested using Schoenfeld residuals. Kaplan-Meier plots will allow visual comparisons between the groups. Analyses will be undertaken on an intention to treat basis. Stata 15 (Stata Corp. College Station, TX, USA) will be used for statistical analyses.

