### Methods in analysis to handle protocol non-adherence and any statistical methods to handle missing data {20c}

All participants will be included in the main analysis (intention to treat) regardless of dropout or adherence to the intervention. Only those who withdraw from the study and all their collected data will be excluded from the analysis. Missing data on the secondary outcomes will be handled by multiple imputation if missingness is found to be “completely at random” and > 10%.

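### The unblinding section lets unblinded care staff have a participant's data removed without tying this to the participant's own request; it must be reconciled with intention to treat and the withdrawal rule

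*Protocol article*

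**What the plan says.** Four parts of the Protocol article bear on whose data leave the analysis.

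- **Procedure for unblinding {17b}.** The section calls unblinding not applicable because "those responsible for the healthcare of the participant are not blinded to the group assignment". It adds that these staff "can inform the statistician to remove data related to a participant with a particular participant number". No ground, participant request, time limit or record is mentioned.
- **Protocol non-adherence and missing data {20c}.** "All participants will be included in the main analysis (intention to treat) regardless of dropout or adherence to the intervention". The one exception follows: "Only those who withdraw from the study and all their collected data will be excluded from the analysis".
- **Discontinuing or modifying interventions {11b}.** The choice about data belongs to the withdrawing participant: "Participants who withdraw from the study are provided with the option of (a) all their collected data being withdrawn from the study", or having the collected data used.
- **Sequence generation {16a} and statistical methods {20a}.** Both commit to intention to treat: "An intention-to-treat approach will be used for analysis" and "Analyses will be undertaken on an intention to treat basis".

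Section {17b} refers to neither {11b} nor {20c}, and neither of those refers to it.

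**The concern.** Section {17b} and section {20c} name different actors and different conditions for taking a randomised participant out of the data. In {20c} with {11b}, the participant decides. In {17b}, the treating side can act and no condition is set.

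This matters because the treating side knows the arm and usually the course. Progress and missed sessions are discussed in multidisciplinary meetings ({11c}), and the Limitations section names therapist allegiance to one therapy as a possible bias. The mitigations listed there (supervision, an adherence scale, manuals) do not cover data removal. Blinding of the outcome assessors ({17a}) gives no protection if a whole record is taken out. A removal that depends on arm and outcome shifts the primary hazard ratio in whichever direction the removals fall.

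A secondary matter is that the primary outcome is read from ED records ({18a}), which need no contact with the participant. Section {11b} does not say whether someone who withdraws from therapy and questionnaires may still allow those records to be used.

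**Working it through.** **Step 1: the rules side by side.**

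| | {17b} | {20c} with {11b} |
|---|---|---|
| Who acts | Care staff who know the arm | The withdrawing participant |
| Condition | None stated | Withdrawal from the study and of all collected data |
| Effect | Participant's data removed | Participant excluded from analysis |
| Cross-reference | None | None to {17b} |

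If every removal under {17b} carries out a choice made under {11b}(a), the columns agree. If any removal can arise otherwise, it breaks the exclusive wording of {20c}. The text of {17b} does not settle which applies.

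**Step 2: the plan's own figures.** Section {14} gives re-presentation of 48% against 24%, a hazard ratio of 0.42 and 132 participants before dropout.

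- HR = ln(1 − 0.24) / ln(1 − 0.48) = 0.420, which agrees.
- Freedman's formula with HR 0.42, 80% power and two-sided 5% gives 47.05 events. Dividing by the mean event proportion of 0.36 gives 131. Rounding up to 48 events first gives 133. The stated 132 is reproduced.

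Neither figure depends on the removal rule.

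**Step 3: how far selective removal could move the result (illustration).** Inputs from the plan are 137 per arm and 48% events, so about 66 events per arm. Assumptions not in the plan are no true effect, and k participants, all with an event, removed from one therapy arm only.

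Apparent HR = ln(1 − (66 − k)/(137 − k)) / ln(1 − 66/137)

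- k = 5: ln(71/132) / ln(71/137) = 0.943
- k = 10: ln(71/127) / ln(71/137) = 0.885

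For the false-positive rate, the log-rank statistic shifts by |ln HR| × √(D/4), with D = 132 − k events.

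- k = 5: shift 0.33, two-sided type I error about 6%
- k = 10: shift 0.68, two-sided type I error about 10%

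**Step 4: fewer observed events.** Section {14} expects 35% to complete 24 months. With exponential event and loss times, the observed event proportion is 0.654/(0.654 + 1.050) × (1 − 0.52 × 0.35) = 0.314, where 0.654 = −ln 0.52 and 1.050 = −ln 0.35. That is about 43 events per arm. The same formula gives HR 0.90 (type I error about 8%) for k = 5 and 0.80 (about 16%) for k = 10. This is rougher than Step 3, because the formula treats a crude proportion as if follow-up were complete.

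**The case against.** The strongest reply is that {17b} is not an exclusion rule. It answers the item on unblinding, says the item does not apply, and mentions in passing how a removal reaches the statistician, namely by participant number. Who is excluded is settled in {20c}, whose wording is exclusive, and {11b} gives the decision to the participant. A reader might infer that the plan authorises staff to initiate exclusions. Nothing in the document says so, and {11b} and {20c} read together point the other way. This stands, and it is why the point is one of reconciliation. It does not remove the point, because {17b} links removal to staff who know the arm, sets no condition and does not refer to the sections that would confine it.

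On follow-up through ED records, a reader might infer that option (b) in {11b} stops at data gathered before withdrawal, or that anyone who stops attending is lost to the primary outcome. The documents support neither reading. Option (b) carries no such limit. Section {18a} searches ED presentations for all study participants over 24 months, and {20c} keeps dropouts in the main analysis. Only formal withdrawal is unclear, and consent documents that are not shown may already cover it.

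The counts of 5 and 10 are also open to attack. The plan gives no expected number of removals, and confining them to re-attempters in one arm is a worst case. That stands too.

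**Conclusion.** The sentence in {17b}, as worded, conflicts with {20c} and with the intention-to-treat commitments in {16a} and {20a}. It should be narrowed. The documents do not show that staff-initiated removal is intended, and it would be wrong to say that the plan has abandoned intention to treat.

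The possible size is illustrative only. With no true effect and one-sided removal of re-attempters, 5 removals give an apparent HR of 0.90 to 0.94 and 10 give 0.80 to 0.88. Type I error is about 6% to 8% and 10% to 16% respectively, depending on whether 48% or 31% of participants have an observed event. Balanced removals, or removals unrelated to outcome, would do far less. The figures of 132, 137 and 411 do not change.

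Deletion at the participant's own request is itself an exclusion after randomisation. It is the participant's right under {11b} and is not disputed. It only needs to be visible by arm.

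**What to change.** 1. Reword {17b} so that data are removed only on the participant's documented request under {11b}(a), and staff responsible for care may not initiate removal. Add cross-references to {11b} and {20c}.
2. Log each removal with its date, and report removals by arm in the CONSORT diagram that the exclusion criteria section already promises. The research assistant already monitors reasons for discontinuation, including withdrawn consent ({18b}), so little new work is needed.
3. Secondary: state in {11b} whether a participant who withdraws from therapy and questionnaires may allow continued use of ED records for the primary outcome. Offer that choice if the consent documents do not already do so.

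Items 1 and 2 cost a few sentences of protocol text. Item 3 may need a small consent amendment through the ethics committee, a route that {25} already provides. The right to full deletion and the sample size are unchanged. The Trial status section reports 12 participants recruited, so the rule can be settled before most data exist.

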### Data collection and management

#### Plans for assessment and collection of outcomes {18a}

Each person who presents to Gold Coast Health is assigned a unique identifying, or UR, number. The Emergency Information System at Gold Coast Health (viz., FirstNet database) records all ED presentations. The ED presentations will be interrogated for the UR number of all study participants, and any presentation within 24 months of an initial presentation will be reviewed for evidence of suicidality. Multivariate Cox proportional hazard regression models will be used to analyse time to re-presentation for a suicide attempt. Time to suicide attempt is measured by calculating the total number of days from the initial presentation (not including days of admission for some consumers with medical and/or psychiatric admission) to the re-presenting date for a subsequent suicide attempt.

For secondary outcomes, data are collected by the RA at five time points: (1) baseline, (2) end of CBT or ASSIP interventions, (3) 6 months, (4) 12 months, and (5) 24 months from baseline. At baseline, demographic data and psychometric data are collected in person or via the telephone with the RA, as outlined below. At end of treatment and 6, 12, and 24 months, psychometric data are collected. Therapeutic alliance is assessed at the completion of the interventions. Cost comparisons will be based on service information regularly collated by GCMHSS and ED (e.g. contact hours, bed stays, ED visits). Study completion will be analysed post hoc, as a secondary outcome.
i)Demographic data: includes age, gender, method of suicide attempt, employment status, education history, place of residence, living situation, marriage status, family contact, known diagnoses and co-occurring conditions (e.g. drug and alcohol use), and history of service provision, including use of psychological interventions

It is anticipated that a number of people within the study population will be from specific cultural groups, who may also be high-risk populations, such as Aboriginal and Torres Strait Islander people, people from cultural and linguistically diverse (CALD) communities, people who identify as LGBTQI, older persons (aged over 60 years), and young people (aged 16–18 years). Questions are included to enable the identification of these specific target population subgroups.
ii)Psychometric data: participants are assessed on their level of suicidality, depression, anxiety, stress, resilience, therapeutic engagement, and their ability to cope and problem solve. The following measures are used.

Columbia Suicide Severity Rating Scale (C-SSRS) [44] is a rating scale that assesses suicide ideation and behaviour. The scale consists of four subscales: severity of ideation (e.g. plan or method), intensity of ideation (e.g. frequency, duration), behaviour (e.g. attempts, preparatory behaviour, non-suicidal self-harm), and lethality (for suicide attempts). The C-SSRS has been used in clinical and non-clinical populations, including adolescents and adults [44], and has been validated in other countries including Korea [45] and Turkey [46]. The C-SSRS has demonstrated convergent and divergent validity with other established suicide assessment scales (i.e. Scale for Suicide Ideation and the Columbia Suicide History Form) [44] and has also shown to have high sensitivity and specificity for suicidal behaviour compared to the other scales [44]. The intensity of the ideation subscale has also demonstrated good internal consistency [44]. The C-SSRS was originally developed by the US Food and Drug Administration to be used in clinical research trials and is currently recommended as the preferred instrument for clinical trials [47]. The C-SSRS takes around 10 min to complete.

Depression, Anxiety and Stress Scale (DASS)-21 [48–50] is the short form of DASS, a self-report scale that aims to measure depression (e.g. dysphoria, hopelessness), anxiety (e.g. situational anxiety, subjective experience of anxious affect), and stress (e.g. difficulty relaxing, feeling nervous, being easily upset). Each subscale (i.e. depression, anxiety, and stress) contains 7 4-point (0–3) Likert scale items. A final score for each subscale is obtained by summation with higher scores indicating higher levels of depression, anxiety, or stress. Scores are multiplied by 2 (to be consistent with scores from the full version of DASS) to give the final score which can range from 0 to 42. The DASS has been used and established in clinical and non-clinical populations and has been shown to have high internal consistency and convergent and divergent validity [48, 51, 52]. The scale takes around 5–10 min to complete.

The Coping Inventory for Stressful Situations (CISS) [53–55] is a 48-item self-report questionnaire that assesses thee different types of coping styles: emotional-orientated, task orientated, and avoidant (distraction and social diversion):
Task-oriented coping: primary control style—the main emphasis is to solve the problem or alter the situation while controlling emotions. This can be helpful when situations are changeable but not helpful for complex social problems.Emotion-oriented coping: secondary control style—the main emphasis is to reduce emotional stress and emotional reactions. Can be helpful in the short-term for situations that are uncontrollable but will be maladaptive in the long term.Avoidant-distracted coping: focuses on pleasurable or distracting activities that helps one avoid the problem or situation. Can be helpful in the short term but will not be helpful over the long term especially for problems that are uncontrollable.Avoidant-social coping: focuses on social diversion as a means of distracting oneself from the problem or situation (or seeking assistance to address the problem or situation). Can be helpful in the short term, but it is more effective to learn how to address problems directly without continually relying on others.

The CISS has shown high internal consistency for clinical and non-clinical samples [55]. The CISS has also demonstrated moderate to high test-retest reliability [55]. Construct validity has been demonstrated through factor analysis work and relationships between the CISS and other measures [55]. The CISS includes separate adolescent and adult forms [55]. Participants are asked to rate each item on a 5-point frequency scale: 1 “not at all” to 5 “very much”. The CISS usually takes around 10 min to complete.

Brief Resilience Scale (BRS) is a 6-item outcome measure designed to assess the ability to bounce back or recover from stress [56]. The BRS is considered to relate more closely to the original meaning of resilience [56]. The BRS has been shown to be a reliable and valid measure of resilience in clinical and non-clinical samples [56, 57], and in a systematic review of resilience measurement scales, the BRS was deemed to have one of the best psychometric ratings [58]. The scale takes around 5 min to complete.

The revised Helping Alliance Questionnaire (HAqII) is a 19-item self-report questionnaire (therapist and patient version) which is an improved version of the 11-item self-rating Penn Helping Alliance Questionnaire (HAq) [59]. It is used to evaluate the quality of the patient–therapist relationship (therapeutic alliance). The HAqII has demonstrated good validity for psychotherapy outcomes, good internal consistency for both patient and therapist (Cronbach’s alpha 0.9–0.93), and good test-retest reliability (test-retest coefficient patient 0.78; therapist 0.56) [59]. The HAqII demonstrated high convergence with another, widely used self-report measure of alliance California Psychotherapy Alliance Scale (CALPAS) total score (patient version: *r* = 0.59–0.69 and therapist version: *r* = 0.75–0.79) [59]. The questionnaire takes around 10 min to complete.

Independent-Interdependent Problem-Solving Scale (IIPSS): the IIPSS assesses problem-solving preference: independent problem-solving (e.g. problem-solving without relying on others’ assistance) and interdependent problem-solving (problem-solving relying on others’ assistance). The scale has good reliability, with a single factor structure (eigenvalue = 3.96) and good internal consistency (Cronbach’s *α* = .77 and .80) [60]. The scale also has good convergent validity (relationship with Relational-Interdependent Self-Construal Scale and Extraversion Scale) and good predictive validity (predicting student’s likelihood of either finding a solution online or asking another student for help) [60].

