#### Exclusion criteria

The following are the exclusion criteria: decline of, or inability to, consent; inability to consent may include a significant language or speech problems, acute psychosis/thought disorder, cognitive impairment, or significant developmental disorder (e.g. learning disabilities, autism, dementia); and people with a currently clinically relevant diagnosis of borderline personality disorder are excluded, as ASSIP is not recommended for consumers with a history of complex trauma ([name] 2018, developer of ASSIP); however, clinicians can refer at their own discretion following an MDT discussion.

People who are already receiving specialised psychological interventions or who are taking psychotropic medication will still be able to participate in this study. We follow a pragmatic study design model [32], with the study being conducted in a busy “real-world” mental health setting to test the applicability of these interventions to consumers from different backgrounds, including previous service use and treatment plans. Information about dropout for each individual (including reasons for dropping out) is being collected for this study and defined as a participant who completes the baseline assessment (conducted at the same time as the formal consent process), but does not attend any of the follow-up assessment or treatment sessions since that. If a person has been rebooked three times or more and does not attend, they will be considered as someone who has dropped out of the study; that person is then discussed in MDT (e.g. for referral back to the Acute Care Team if appropriate). A CONSORT diagram will be provided in the publication of results [33].

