#### Intervention description {11a}

##### Attempted Suicide Short Intervention Program (ASSIP)

ASSIP is a manualised brief therapy composed of three therapy sessions following a suicide attempt and subsequent follow-up over 2 years with personalised mailed letters [23]. The first session consists entirely of a video-recorded, narrative interview with the consumer relating the personal story of how the point of attempting suicide was reached. The second session involves the therapist and consumer watching the video of the recorded session together and collaboratively reflecting on the suicidal dynamic in a safe environment. Automatic thoughts, emotions, psychological pain and stress, and contingent behaviour are discussed. A psycho-educative handout and homework are given to consumers. The third session starts with a discussion of the homework. This is followed by jointly formulating the ASSIP case conceptualisation. A credit card size leaflet (i.e. a leporello) is provided on which is printed the agreed long-term goals, individual warning signs, and safety strategies. A second card is provided with crisis contact phone numbers. These sessions are followed by letters, which asks consumers how things were going [38]. These letters (written by the therapist) are sent regularly over 24 months (i.e. every 3 months in the first year, and every 6 months in the second year) [38].

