##### Brief Cognitive Behavioural Therapy (CBT) for Suicide Prevention

This is a manualised approach involving brief CBT for suicide in six 60-min sessions and has been adapted by the research team. After a comprehensive search of the literature, various online CBT resources were accessed to create the manual. More specifically, permission was obtained from two authors who had created and published CBT manuals for the treatment of suicide: the Pakistan Institute of Living and Learning [41] and Stewart [42]. The elements of both these manuals were taken to create the Brief CBT for Suicide Prevention manual used for this study. The Brief CBT for Suicide Prevention incorporates skills development and emphasises internal self-management [24]. The therapy focuses on the identification of internal, external, and/or thematic triggers for suicidal thinking and behaviours, as well as factors that maintain the desire to suicide, using thought records and/or chain analyses. The brief CBT for Suicide Prevention aims to challenge distortions and misconceptions, including core beliefs that interfere with the motivation to initiate the process of problem-solving and distress tolerance, by working on acceptance of emotional and/or physical pain. The final phase of the brief intervention focuses on relapse prevention [43].

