#### Secondary outcome measures

Self-reported levels of suicidality, depression, anxiety, stress, resilience, problem-solving skills, and self- and therapist-reported level of therapeutic engagement are measured. Scores will be compared for each group at each follow-up time point. A cost comparison will also be done for both interventions (compared to TAU), and estimates will be based on service information regularly collated by GCMHSS and ED (e.g. contact hours, bed stays, ED visits). We expect a low completion rate (see the “Sample size” section). Study completion will be analysed post hoc, as a secondary outcome.

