**Fig. 1 Fig1:**
[figure not shown]
SPIRIT figure—ASSIP-CBT study schedule of recruitment, interventions, and baseline and follow-up assessments. *For all participants, including SPP. **Includes ASSIP follow-up letters sent over 24 months after therapy. ***This includes employment status; cultural and linguistically diverse (CALD) status; Aboriginal and Torres Strait Islander and lesbian, gay, bisexual, transgender, intersex, and queer (LGBTQI) status; education history; living situation; known diagnoses; and history of service provision

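### The second assessment is timed by the end of CBT or ASSIP rather than from baseline, so the between-group comparison of secondary scores at that visit is open to bias

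*Protocol article*

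**What the plan says.** All references are to the protocol article.

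- Plans for assessment and collection of outcomes {18a} gives five time points for the secondary outcomes. After baseline they are "2) end of CBT or ASSIP interventions, (3) 6 months, (4) 12 months, and (5) 24 months from baseline". No week or window is attached to the second.
- The same section confirms what is measured then: "At end of treatment and 6, 12, and 24 months, psychometric data are collected". It also says "Therapeutic alliance is assessed at the completion of the interventions".
- Secondary outcome measures commits to a comparison at all of these visits: "Scores will be compared for each group at each follow-up time point".
- The intervention descriptions give ASSIP as "composed of three therapy sessions following a suicide attempt" and the other therapy as "brief CBT for suicide in six 60-min sessions". Neither states the interval between sessions.
- Objectives {7} names two contrasts for primary and secondary outcomes, each therapy plus SPP against SPP alone. Hypotheses adds ASSIP against CBT and calls it exploratory.
- Participant timeline {13} refers to Fig. 1 for the schedule. One footnote to that figure reads "For all participants, including SPP", but without the figure one cannot tell which item it marks.

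**The concern.** Four of the five assessments share a clock that starts at baseline. The second is set by an event that happens after randomisation and depends on the arm. Participants are approached 48 to 72 hours after the event, so this visit probably falls early, when scores may still be changing with time alone. If so, an arm measured later would tend to look better whatever its treatment did.

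A second difficulty lies within the therapy arms. A participant who stops early, or whose sessions are moved, has no clear end-of-intervention date, yet the analysis is by intention to treat.

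At stake is the earliest comparison of the psychometric outcomes, probably the best attended. At the 4.5% monthly dropout assumed in Sample size {14}, about 0.955^6 = 76% would remain at 6 months and fewer later. A visit made at the wrong time cannot be fully repaired in the analysis.

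**Working it through.** The plan states no figure on this point, so there is none to reproduce. The check has two parts.

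**1. The stated timing, side by side**

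| Arm | What sets assessment 2 | Time from baseline in the readable text |
|---|---|---|
| ASSIP + SPP | end of three sessions | not given |
| CBT + SPP | end of six sessions | not given |
| SPP | no CBT or ASSIP to end | not given (Fig. 1 not shown) |

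Assessments 3 to 5 are at 6, 12 and 24 months from baseline in every arm.

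Take the end of therapy as sessions × interval. The ends coincide only if 3 × (ASSIP interval) = 6 × (CBT interval), that is, if CBT sessions are spaced at half the ASSIP interval. Otherwise the two ends differ, and a single SPP date cannot match both.

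**2. An illustration of size, ASSIP versus CBT only**

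The documents supply only the session counts (3 and 6) and 137 per arm. Everything else here is assumed:

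- sessions are weekly, so therapy ends at about weeks 3 and 6;
- both arms follow the same recovery, with the remaining excess score at week t equal to A × 0.5^(t/h);
- total recovery A is 0.5 to 1.0 SD, and half-life h is 4 to 8 weeks.

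The spurious difference is A × [0.5^(3/h) − 0.5^(6/h)]:

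| A (SD) | h (weeks) | Calculation | Difference (SD) |
|---|---|---|---|
| 0.5 | 8 | 0.5 × (0.771 − 0.595) | 0.09 |
| 0.5 | 4 | 0.5 × (0.595 − 0.354) | 0.12 |
| 1.0 | 8 | 1.0 × (0.771 − 0.595) | 0.18 |
| 1.0 | 4 | 1.0 × (0.595 − 0.354) | 0.24 |

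With 137 per arm and full attendance, the standard error of a difference in SD units is √(2/137) = 0.121. A 5% two-sided test would then reject in about 11% (at 0.09 SD) to 51% (at 0.24 SD) of trials with no true difference. With fewer attending, these percentages fall.

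**Sensitivity.** Suppose the first session is at week 0. Weekly sessions then end at weeks 2 and 5, and fortnightly sessions at weeks 4 and 10. With half-lives of 4 to 12 weeks, the range is:

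- lowest (weekly, A = 0.5, h = 12): 0.5 × [0.5^(2/12) − 0.5^(5/12)] = 0.07 SD;
- highest (fortnightly, A = 1.0, h = 4): 0.5^(4/4) − 0.5^(10/4) = 0.32 SD.

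If spacing equalises the end dates, the difference is zero.

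**Against SPP** there is no SPP date to enter, so neither the size nor the direction can be computed.

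**The case against.** The strongest reply has four parts.

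- **Fig. 1 may settle the SPP date.** The article sends the reader there for the schedule, and the footnote suggests that some item applies to SPP too. This stands. A reader might infer that SPP has no second assessment, or that its comparison is confounded as a matter of fact. The documents do not support either, because the figure was not available. It does not dispose of the point: if assessment 2 follows the end of therapy, one SPP date cannot match two different therapy ends, and if the figure fixes one week for everyone, the text in {18a} disagrees with it.
- **Different end dates are inferred.** This also stands. Three against six sessions makes a gap likely, but no interval is given.
- **The illustration covers the exploratory contrast and rests on an assumed recovery curve.** This stands. The idea of early recovery fits suicidality and distress scores better than coping style, resilience or problem-solving preference, for which the documents give no reason to expect rapid change.
- **An end-of-treatment visit is a legitimate choice.** It is, and therapeutic alliance has to be measured then. The difficulty is only the between-group comparison attached to it.

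A further tempting reading is that rebooking delays the visit in the therapy arms alone. The clause under Exclusion criteria, "If a person has been rebooked three times or more and does not attend", follows a dropout definition that covers follow-up assessments as well as treatment sessions. It therefore does not show this. It also counts such a person as having dropped out, which limits how far a visit can drift.

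**Conclusion.** The point holds in a limited form. The article joins an arm-dependent, post-randomisation visit date to a planned comparison of groups at that visit. This is a stated choice, more than a detail left to another document. Unless session spacing equalises the end dates, arm and time since the attempt are mixed there.

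The comparison is open to bias; the documents do not show that it is biased. The size is unknown. The 0.09 to 0.24 SD depends wholly on the assumed weekly sessions and recovery curves and concerns only the exploratory ASSIP versus CBT contrast.

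The reach is narrow: secondary psychometric scores at one of four follow-ups. A reader might extend the concern to the main result, but the primary outcome is taken from emergency department records and does not depend on this visit. The 6-, 12- and 24-month assessments share a clock from baseline in all arms. No sample size or power figure is touched.

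**What to change.** Set assessment 2 at one fixed number of weeks from baseline, with the same window in all three arms, and make the text in {18a} agree with Fig. 1. If the figure already fixes a common week, correcting the text is enough. Treatment itself need not change.

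If an end-of-therapy visit is kept, for example for therapeutic alliance, report it descriptively within the therapy arms and leave it out of between-arm comparisons. Limit the sentence under Secondary outcome measures to the visits on the common clock.

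The cost is a visit window and a line or two of wording. The small downside is that some participants will be assessed a little before or after their therapy ends. Trial status reports 12 of 411 recruited (12/411 = 3%), so a change made at that stage would cover nearly the whole sample.
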